### Intervention

We invite the training group to participate in an exercise program that we have specially designed for pregnancy, including aerobic activity, specific exercises for stabilization of the lower back and pelvis, and strength exercises for the pelvic floor muscles that we have specially designed for pregnancy. We conduct training groups for a total of 60 minutes four times weekly at the hospital. We ask the women to come to exercise training a minimum of twice weekly between 14 and 37 weeks of gestation. We also encourage the women to come for exercise training even after week 37. The endurance training consists of a 10 minute warm-up followed by walking on treadmills for 25 minutes. The intensity will be moderate, reaching ~80% of their

[figure not shown]

maximal capacity in periods (corresponding to Borg scale 12-15) [18].

In addition, we instruct intervention women in a 50 minute home exercise program which we encourage them to complete at least once per week (35 minutes endurance training and 15 minutes strength exercises). We also teach pelvic floor muscle exercises to do daily. We also recommend the women to be physically active in every-day life. Adherence is strongly emphasized and registered in the women's personal training diary and the reports from the persons leading the training groups. During the training period, the subjects will go through motivational interviewing [19]. This is a client-centred therapeutic method to enhance readiness for change and to elicit the client's own motivations for change. Each woman will go through a 30 minute session of motivational interviewing in each trimester. They will also receive a weight gain curve that shows the recommended weight gain throughout pregnancy,

based on 2009 Institute of Medicine guidelines [20]. The training protocol follows recommendations from the Norwegian Health Directory [21] and the American College of Obstetrics and Gynecology [6]. Specific adjustments are made to the exercise program if needed (for example by using a stationary bike instead of treadmill walking and by modifying the strength exercises to the actual strength level of the participants).

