Women in the control group will receive the customary regular consultations with midwife, general practitioner or obstetrician. They are not discouraged from exercising on their own. Neither group will receive special recommendations about diet, beyond what is given through standard antenatal care. In Norway, the pregnancy care is free of charge. Routine prenatal visits are done by general practitioners, midwives, or a combination of the two, and are usually undertaken in gestational weeks 8-12, 24, 28, 32, 36, 38, 40, and 41. In addition, women are invited to an ultrasound scan is

gestational week 18. There is currently no knowledge about the actual advices about physical activity that pre-natal care providers give to pregnant women, but the guidelines from the Norwegian Health Directory [21] are in line with the international guidelines [6].

Study assessment visits

We will see women for research visits at baseline (12-16 weeks of pregnancy), and again in week 37 (range 36-38), as well at three months post partum (Figure 2). We also obtain clinical measures that are collected during the delivery hospitalization as well as through primary care.

Primary outcome measure

The primary outcome measure is gestational weight gain, calculated as the difference between weight measured at the time of inclusion and weight just before delivery. We measure maternal body weight at enrolment and before delivery to the nearest 0.1 kg with a calibrated electronic scale (SECA 770, Medema, Norway) with participants wearing indoor clothing, without

shoes. Hospital staff will measure weight during the delivery hospitalization using a different scale than at baseline. We will calibrate the scales to ensure comparability. If the hospital staff forget to weight the women, we will use their self-reported weight at the time of delivery as the outcome measure.

Secondary outcome measures

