#### Blinding

Baseline measurements, except for the armband registration of physical activity, will be done before randomisation. Later assessments will be done both blinded (echocardiography, pelvic floor assessments, blood analyses, all offspring variables) and non-blinded to group allocation (weight, skinfold measurements, lumbopelvic pain, oxygen uptake and endothelial function recordings). Although endothelial function recordings are

done non-blinded, the analyses of these data will be done blinded to both group allocation and time of measurement.

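### A forgotten delivery weight is replaced by the woman's own report in the primary outcome, which opens a route for misreporting that could differ by arm

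*Protocol*

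**What the plan says.** The Protocol, under Primary outcome measure, defines the endpoint as "gestational weight gain, calculated as the difference between weight measured at the time of inclusion and weight just before delivery". The intended standard is a scale reading: "We measure maternal body weight at enrolment and before delivery to the nearest 0.1 kg with a calibrated electronic scale". The delivery weight comes from the ward: "Hospital staff will measure weight during the delivery hospitalization using a different scale than at baseline". The scales are to be calibrated so that the two readings can be compared. The fallback follows directly: "If the hospital staff forget to weight the women, we will use their self-reported weight at the time of delivery as the outcome measure".

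Three other places bear on it.

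- **Intervention.** Of the training arm it says: "They will also receive a weight gain curve that shows the recommended weight gain throughout pregnancy". It adds: "Each woman will go through a 30 minute session of motivational interviewing in each trimester". The account of the control arm describes customary consultations and mentions neither element.
- **Blinding.** Later assessments are listed in part as "non-blinded to group allocation (weight, skinfold measurements, lumbopelvic pain, oxygen uptake and endothelial function recordings").
- **Study assessment visits.** A late research contact is already planned: "We will see women for research visits at baseline (12-16 weeks of pregnancy), and again in week 37 (range 36-38").

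Statistical methods plans a linear mixed effects model for outcomes over time. The Protocol sets no limit on the self-report rule and does not put a measured weight in its place.

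**The concern.** The Protocol takes care to make two scales agree and then admits, on equal terms, a value that cannot be calibrated. Because the baseline weight is a scale reading, an error in the self-reported delivery weight passes in full into that woman's gain. It does not cancel within the woman.

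Error of the same size and frequency in both arms would leave the arm difference unbiased on average and mainly add noise. The worry is error that differs by arm. Participants in a comparison of exercise with usual care know their allocation. Only one arm is described as being shown a recommended weight trajectory and coached towards it. A woman in that arm may feel some pressure to report a weight near the curve, which would lower apparent gain with training, as the primary hypothesis predicts. Analysis by randomised arm and adjustment for age, parity and BMI would not remove such an error.

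The number of affected women depends on how often staff forget, which the design does not control.

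**Working it through.** **Inputs from the Protocol (Sample size).** Difference 6 kg; 5% significance level, taken as two-sided; power 0.90; 59 per group; 15% drop-out; 75 enrolled per arm. No SD is stated.

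**Step 1: recover the SD.** For a two-sample comparison of means (normal approximation), n per group = 2 × (SD/6)² × (1.960 + 1.282)². An SD of 10 kg gives 58.4, rounded up to 59, which reproduces the planned figure. Solving with n = 59 gives SD = 6 / [√(2/59) × 3.242] = 10.05 kg. I use 10 kg; it is back-solved, not stated.

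**Step 2: standard error of the arm difference.** SE = 10 × √(2/59) = 1.84 kg.

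**Step 3: bias.** Let f be the share of women whose outcome is self-reported, taken as equal in both arms, and b the between-arm difference in mean misreporting. Then bias = f × b. The Protocol gives neither f nor b, so both are assumed.

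**Step 4: type I error.** With no true effect, the rejection probability is P(Z > 1.96 − bias/SE) + P(Z < −1.96 − bias/SE). It is the same for either sign of the bias.

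| f (assumed) | b (assumed) | Bias | Share of 6 kg | Two-sided type I error |
|---|---|---|---|---|
| 5% | 1 kg | 0.05 kg | 0.8% | 5.0% |
| 10% | 2 kg | 0.20 kg | 3.3% | 5.1% |
| 20% | 2 kg | 0.40 kg | 6.7% | 5.5% |
| 30% | 3 kg | 0.90 kg | 15% | 7.8% |

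Worked for the last row: 0.90/1.84 = 0.489; P(Z > 1.471) + P(Z < −2.449) = 0.071 + 0.007 = 0.078. With 64 per arm (75 × 0.85, rounded), the SE is 10 × √(2/64) = 1.77 kg and the same row gives 8.0%.

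**Step 5: scale.** At SE 1.84 kg, significance needs an observed difference of about 1.96 × 1.84 = 3.6 kg. The largest bias in the table is a quarter of that. If only scale weights are used, this source of bias is zero.

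**The case against.** The strongest reply is that the rule is written as an exception for forgetting. If it applies to one woman in twenty, the table shows almost no effect. That stands, and it limits how serious the point can be.

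A reader might infer that the error does differ by arm and does favour training. The Protocol does not support this. It shows a route, not an occurrence. The curve and the interviews could equally make trained women follow their weight closely and report it more accurately; if controls then under-reported more, the bias would run against training.

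The Blinding section lends less weight than it seems to. It concerns later assessments, scale weight among them, and does not discuss participants' reports. Scale weights remain unblinded after any fix, though a reading to 0.1 kg leaves much less room for distortion.

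The week-37 visit is not a perfect substitute. It is planned, but attendance is not assured: 15% drop-out is expected, and some women may deliver before the visit. The text names weighing at enrolment and before delivery. Weight appears among the later assessments under Blinding without a time point, and the figure with the schedule is not shown. Weighing at week 37 is therefore likely but unconfirmed. The visit may also precede delivery by weeks, since routine antenatal visits run to week 41.

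Finally, counts of self-reported values and sensitivity analyses commonly belong in a statistical analysis plan, which is not at hand, so their absence is no finding. The substitution rule itself is written into the Protocol and remains open to criticism.

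**Conclusion.** The point holds as a weakness in a stated rule: the primary outcome accepts an uncalibrated report from a woman who knows her arm as equal to a scale reading. Bias that differs by arm is possible; its presence and direction are unknown. Over the assumed range its size runs from 0.05 kg to 0.9 kg against a design difference of 6 kg, and type I error from essentially 5% to about 8%. These figures rest on assumed values of f and b, an equal self-report share in both arms, and an SD of about 10 kg implied by the sample size.

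It would be tempting to conclude that the primary test is materially anti-conservative. That needs both frequent forgetting and a large arm difference in misreporting, and the Protocol gives evidence of neither. The rule should be fixed because a better source is close at hand and the change is cheap, but it does not by itself invalidate the primary comparison.

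**What to change.** Replace the self-report sentence under Primary outcome measure with a rule along these lines:

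1. Only scale-measured weights enter the primary analysis; a forgotten delivery weight is treated as missing.
2. Weight is taken on the research scale at the existing week-37 visit (range 36-38), stated explicitly.
3. Baseline, week-37 and delivery weights are fitted together in the planned mixed model, with gestational age at measurement, so that a woman without a delivery weight contributes through her measured late-pregnancy weight.
4. The source of each delivery weight is recorded. Self-reported weights are used only in a labelled sensitivity analysis, with the number per arm reported.

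**Cost.** One paragraph of text and at most one extra scale reading at a visit already planned. The model assumes that missing delivery weights are missing at random given the measured weights and gestational age, which is reasonable when the cause is staff forgetting but should be stated. Precision falls slightly. Women who miss the week-37 visit or deliver before it, and have no delivery weight, contribute only their baseline weight.

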#### Sample size

Based on prior studies [37,38], the power calculation has taken into account a 6 kg expected and clinically relevant difference between mean weight increases in the control group compared to the training group (between baseline and delivery). Based on this assumption, an independent samples t-test, 5% level of significance and test strength of 0.90, gives a study population of 59 in each group. A 15% estimated drop-out requires a total of 150 included obese pregnant women, 75 enrolled in each arm.

#### Ethical considerations

The Regional Committee for Medical Research Ethics has approved the study, and it will be conducted in accordance with the Declaration of Helsinki. All mothers will give their informed, written consent to participate.

#### Blinding

Baseline measurements, except for the armband registration of physical activity, will be done before randomisation. Later assessments will be done both blinded (echocardiography, pelvic floor assessments, blood analyses, all offspring variables) and non-blinded to group allocation (weight, skinfold measurements, lumbopelvic pain, oxygen uptake and endothelial function recordings). Although endothelial function recordings are

done non-blinded, the analyses of these data will be done blinded to both group allocation and time of measurement.

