The maternal secondary outcome measurements are outlined in Figure 2 and described more in detail below. Blood sampling for fasting glucose concentrations and the other blood markers will be taken after a 10 hour overnight fast, and glucose tolerance will be measured by a 2 hour 75 mg per-oral glucose tolerance test. Gestational diabetes is diagnosed as fasting glucose  $\geq 6.9$  mmol/L or 2 h concentration  $\geq 7.8$  mmol/L [22]. Insulin resistance will be calculated using the homeostasis model assessment (HOMA-IR). We will analyse fasting blood for concentrations of lipids, ferritin, haemoglobin, high-sensitive C-reactive protein, and insulin c-peptide. We will also collect whole blood and serum to be frozen at -80C and stored in a biobank for

[figure not shown]

later analyses of hormones associated with female reproduction and blood markers associated with adiposity and insulin resistance. We will also collect Tempus blood RNA tubes and urinary samples to be frozen for later analyses.

Body height will be measured by a wall mounted height scale. Body composition will be assessed by skinfold thickness during pregnancy and also by dual energy x-ray absorptiometry (DEXA-scan) at three months postpartum. Skinfold thickness will be measured at the right side of the body at the following sites: triceps, biceps, and subscapular, by Harpenden Caliper (Holtain Ltd, UK). Sum of skinfold thickness are measured and used for later calculation of body fat percentage. Waist circumference is measured at all time points at the level of the umbilicus. DEXA (Hologic Discovery-A: Integrity Medical Systems) will be used to measure body composition after 10 hours of fasting, to decrease large variations in hydration status (postpartum only).

Lumbopelvic pain (Disability Rating Index) and physical examination of lumbar spine and pelvic region are done by experienced physical therapists. Tests used are active straight leg raising [23] and the posterior pelvic pain provocation test [24].

Prevalence and severity of urinary- and fecal incontinence will be assessed by questionnaires [25,26], muscle strength measurements, 2D and 3D ultrasound investigation of the pelvic muscles, and clinical examination and palpation of the pelvic floor muscles. Pelvic floor muscle strength, and vaginal squeeze pressure, will be measured using a vaginal balloon catheter with a balloon size of 6.7 × 1.7 cm connected to a pressure transducer [27].

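### The primary outcome and several examiner-dependent outcomes are declared non-blinded without a reason, although delivery weighing and the reading of treadmill data could be blinded, at least in part, with little effort

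*Protocol*

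**What the plan says.** The Blinding section places all baseline measurements before randomisation, apart from the activity armband. It then divides the later ones.

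- Blinded: "Later assessments will be done both blinded (echocardiography, pelvic floor assessments, blood analyses, all offspring variables".
- Open: "non-blinded to group allocation (weight, skinfold measurements, lumbopelvic pain, oxygen uptake and endothelial function recordings".
- Endothelial recordings are made open, but "the analyses of these data will be done blinded to both group allocation and time of measurement".

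No reason is given for the open group. The entry for weight does not separate the delivery weight from any weight taken at a research visit, so as written it covers both.

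Under Primary outcome measure, gestational weight gain is "calculated as the difference between weight measured at the time of inclusion and weight just before delivery". Weight is read "to the nearest 0.1 kg with a calibrated electronic scale". The final weight comes from the ward: "Hospital staff will measure weight during the delivery hospitalization using a different scale than at baseline". The scales are to be calibrated against each other. If the ward omits the weighing, the woman's own report of her weight is used.

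Under Secondary outcome measures, skinfolds are taken with a caliper, and "physical examination of lumbar spine and pelvic region are done by experienced physical therapists". The treadmill test records oxygen uptake continuously and blood lactate at the end of each stage. The Objectives list submaximal oxygen uptake and lactate threshold among the outcomes.

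**The concern.** The plan protects many secondary outcomes from knowledge of the arm but not its primary one. It also treats similar measurements differently. Offspring skinfolds fall in the blinded group and maternal skinfolds in the open one. Hands-on pelvic floor examination is blinded and hands-on lumbopelvic examination is not. Endothelial recordings get a blinded reading, and no such step is stated for the treadmill data.

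The hypotheses in the Objectives are directional, and caliper readings, provocation tests and a threshold derived from stage-by-stage lactate values all leave room for judgement. An assessor who knows the arm could move them towards the hypothesis without intending to.

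For weight, the scale leaves little room for judgement. The more plausible route is the choice between a measured and a self-reported value. If weighing staff know the arm, the fallback could be used more often in one arm. The woman supplying the replacement value knows her arm, and only the exercise arm receives a recommended weight-gain curve and motivational interviewing (Intervention section).

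**Working it through.** **Where blinding is possible on the protocol's own account**

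| Outcome | Stated status | What the protocol offers |
|---|---|---|
| Delivery weight | open | Taken by hospital staff; no reason is given why they must know the arm, and nothing says that they do not |
| Submaximal oxygen uptake, lactate threshold | oxygen uptake open; lactate threshold not named | Recorded data that can be coded, as for endothelial function |
| Maternal skinfolds | open | Offspring skinfolds are blinded, but the assessor is not identified |
| Lumbopelvic tests | open | Pelvic floor assessment is blinded; no statement that the same people could do both |
| Endothelial function | recorded open, read blinded | Already handled |

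Only the first two rows can be changed without assuming anything about staffing.

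**Inputs**

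- n = 59 per arm, difference 6 kg, 5% level, power 0.90 (Sample size section).
- SD: not stated. The two-sided normal formula n = 2(1.960 + 1.282)² × SD²/6² with SD = 10 gives 2 × 10.51 × 100/36 = 58.4, so 59. An SD of 10 kg therefore returns the protocol's figure and is used here as an assumption, with 8 kg as an alternative.
- Size of the false shift: assumed throughout.

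**Type I error for weight**

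Standard error of the difference = SD × √(2/59): 1.84 kg at SD 10 and 1.47 kg at SD 8. With shift b and z = b/SE, the two-sided rejection probability when there is no true effect is 1 − Φ(1.96 − z) + Φ(−1.96 − z).

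| Assumed shift | SD 10 kg | SD 8 kg |
|---|---|---|
| 0.25 kg | 5.2% | 5.3% |
| 0.5 kg | 5.9% | 6.3% |
| 1 kg | 8.4% | 10.4% |
| 2 kg | 19.2% | 27.4% |

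For example, 0.5 kg at SD 10 gives z = 0.5/1.84 = 0.27, and 1 − Φ(1.69) + Φ(−2.23) = 0.046 + 0.013 = 0.059.

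**The self-report route**

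If a share f of the exercise arm has self-reported weights that are too low by u kg, with no such error among controls, the mean shift is f × u. With f = 0.1 and u = 1 it is 0.1 kg (type I error about 5.0%). With f = 0.3 and u = 2 it is 0.6 kg: z = 0.6/1.84 = 0.33, and 1 − Φ(1.63) + Φ(−2.29) = 0.051 + 0.011, about 6.2% at SD 10. Both f and u are assumed.

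**Examiner-dependent secondary outcomes**

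Rejection probability of a two-sided 5% t-test with 59 per arm:

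| Assumed shift (SD units) | 0.10 | 0.15 | 0.20 | 0.25 |
|---|---|---|---|---|
| Type I error | 8.4% | 12.7% | 19.0% | 27.0% |

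The 59 was derived for weight. Using it for other outcomes is a further assumption.

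**The case against.** The strongest reply is that the Blinding section openly discloses a design choice and contradicts nothing. The primary outcome is also a poor target for observer bias. Baseline weight precedes randomisation, and the later weight is read to 0.1 kg on a scale that is to be calibrated. On this scale the upper assumed shifts would mean a systematic reading error of 1.0 to 2.5 kg (0.10 to 0.25 of an SD of 10 kg), which is not credible. This stands, and it keeps the point small for weight.

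It is also fair that blinding would be incomplete. Women may disclose their arm. Blinded reading of treadmill files does not stop staff encouraging one arm more during the test. The Disability Rating Index, if the woman completes it herself (the protocol does not say), cannot be blinded by changing the assessor. That ward staff might weigh selectively by arm is a possibility; the protocol speaks only of forgetting.

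A reader might infer that the trial already has the people and procedures to blind everything on the open list at no cost, for instance by having the pelvic floor assessor also take skinfolds and lumbopelvic tests. The documents do not support that. They give no staffing list, no assessor duties and no costs. A longer session on lumbopelvic symptoms could reveal the arm to an assessor who is now blinded. A weight taken at week 37 would not help the primary comparison either, because that outcome uses the weight just before delivery.

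Disclosing the choice does not reduce the bias, however. The two changes that need no staffing assumption remain available.

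**Conclusion.** The point holds in a limited form. The protocol leaves its primary outcome and several examiner-dependent outcomes open without a reason. For delivery weight and treadmill-derived readings, knowledge of the arm can be reduced with instructions and with a procedure the protocol already uses for endothelial data.

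For weight the likely effect is small: about 6% type I error under an assumed 0.5 kg shift, an assumed SD of 10 kg and 59 per arm. The 8-27% range belongs only to examiner-dependent secondary outcomes under assumed shifts of 0.10 to 0.25 SD. It should not be read as the error rate of the primary test. No bias size can be taken from the documents, and the text is not self-contradictory.

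**What to change.** Amend the Blinding section as follows.

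1. **Delivery weight.** State who weighs the women, and keep those staff unaware of the allocation as far as possible: do not display the arm to them, and ask women not to disclose it. This also limits arm-dependent use of the self-report fallback. Record for each woman whether the weight was measured or self-reported, so that its use can be compared between arms.
2. **Treadmill data.** Derive submaximal oxygen uptake and lactate threshold from coded files, blinded to arm and visit, as is already planned for the endothelial recordings.
3. **Skinfolds and lumbopelvic tests at week 37.** Use blinded assessors if existing staff allow it without exposing assessors who are now blinded. Otherwise give the reason for leaving these open.

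The first item costs an instruction to the ward and to participants, plus one recorded field. The second costs some file coding. Neither changes the sample size. Disclosure by women, encouragement during the test and the error in self-reported weight itself would remain, and the protocol should say so.
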